| Bilirubin (total)                                                                         | x                            |  |  | x                          |   | x   |                                                                                                                                                                                                    |     | x   |     |     | x                                                                                                      |

A prospective phase I/II study to investigate the feasibility, safety and efficacy of IL-15 activated cytokine induced killer (CIK) cells in relapsing patients with acute leukemia or myelodysplastic syndroms after allogeneic stem cell transplantation.  
Version 2.0 dated 01.02.2015

|                            |     |  |  |       |       |       |       |       |       |  |  |         |
|----------------------------|-----|--|--|-------|-------|-------|-------|-------|-------|--|--|---------|
| Immune status              | (x) |  |  | $x^2$ | $x^2$ | $x^2$ | $x^2$ | $x^2$ | $x^2$ |  |  | (x)     |
| Cytokine profile           |     |  |  | $x^2$ | $x^2$ | $x^2$ | $x^2$ | $x^2$ | $x^2$ |  |  |         |
| NKG2D receptor             |     |  |  | $x^2$ | $x^2$ | $x^2$ | $x^2$ | $x^2$ | $x^2$ |  |  |         |
| Chimerism                  | x   |  |  |       |       | $x^3$ |       |       | $x^3$ |  |  | x       |
| BCR-ABL                    | (x) |  |  |       |       | (x)   |       |       | (x)   |  |  |         |
|                            |     |  |  |       |       |       |       |       |       |  |  |         |
| Bone marrow assessments    |     |  |  |       |       |       |       |       |       |  |  |         |
| Morphology/Histology       | x   |  |  |       |       | $x^4$ |       |       |       |  |  | $(x)^5$ |
| Chimerism                  | x   |  |  |       |       | $x^4$ |       |       |       |  |  | $(x)^5$ |
| Chimerism Subpop           | (x) |  |  |       |       | $x^4$ |       |       |       |  |  | $(x)^5$ |
| MRD or                     | (x) |  |  |       |       | $x^4$ |       |       |       |  |  | $(x)^5$ |
| BCR-ABL                    | (x) |  |  |       |       | $x^4$ |       |       |       |  |  | $(x)^5$ |
| Ophtalmologist control     |     |  |  |       |       |       |       |       |       |  |  | $x^6$   |
| Pulmonary function testing |     |  |  |       |       |       |       |       |       |  |  | $x^6$   |
|                            |     |  |  |       |       |       |       |       |       |  |  |         |
|                            |     |  |  |       |       |       |       |       |       |  |  |         |

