| Coordinating investigator                        | [name]. med. [name]
University Hospital Frankfurt, Goethe University
Department for Children and Adolescents
Division for Stem Cell Transplantation and Immunology, Germany                                                                                                                                                                                                                                                                                                                                                                                                                                                                      |
| Planned number of sites                          | 3 sites in Germany                                                                                                                                                                                                                                                                                                                                                                                                                                                                                                                                                                                                                                               |
| Design                                           | Multi-site, non-randomized Phase I/II study involving children and adults.
This is a phase I/II multicenter-study to investigate the feasibility safety and efficacy of interleukin (IL)-15 activated CIK cells in patients with acute leukemia or myelodysplastic syndrome (MDS) showing evidence of relapse after allogeneic stem cell transplantation (SCT). CIK cell infusions will be given with an interval of 4-6 weeks according to a dose escalation schedule in patients with impending relapse after allogeneic SCT. In presence of acute graft versus host disease (aGvHD) $\geq$ grade II, the next scheduled infusion will not be administered. |

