| Study endpoints
Primary endpoints | 
 
• The dose-limiting toxicity based on grade III or IV aGvHD, and
 
• Extensive cGvHD
 
                                                                                                                                                                                                                                                                                                                                                                                                                                                                                                                                                                                                                                                                                                                                                                                                                                                                                                                                                                                                                                                                                                                |

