## **3 Study Design**

This is a phase I/II study to investigate the feasibility, safety and efficacy of IL-15 activated CIK cells in patients with acute leukemia or MDS showing evidence of molecular relapse after allogeneic SCT.

- CIK cell infusions will be given with an interval of 4-6 weeks according to a dose escalation schedule in patients with impending relapse after allogeneic SCT. In presence of aGvHD  $\geq$  grade II, the next scheduled infusion will not be administered. CIK cell infusions will be administered until the patient reaches molecular remission, until a maximum of 8 infusions are reached or until the patient progresses, provided that patients develop no more than grade I aGvHD.

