### **Eligibility requirements for next CIK cell infusion (4-6 weeks after previous CIK cell infusion):**

- No immunosuppression or steroids
- No chemo- or immune therapy, except patients with tyrosine-kinase inhibitors (TKI) for BCR-ABL positive leukemias.

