### **Exploratory Endpoints**

Efficacy:

- Proportion of patients that achieve complete and partial response after 1 year of first CIK cells infusion.
- Progression-free survival and overall survival
- Response duration

Safety Endpoint:

- Proportion of patients who become aGvHD > grade II or extensive chronic GvHD.

CIK cells infusions:

- The dose-limiting toxicity based on grade III or IV acute GvHD

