## Analysis

A descriptive statistics will be performed at the end of the study. An intent-to-treat principle (ITT) or per-protocol analysis will be done.

To analyze the efficacy of CIK cell treatment following factors will be considered:

- Complete and partial molecular response
- rate and duration of complete/partial molecular response following CIK cell administration at the end of CIK cell infusions and after 1 year of first CIK cell infusion
- rate of and time to non response
- rate of and time to relapse with previous partial/complete response
- Progression-Free survival (PFS) and overall survival (OS)
- Cumulative incidences of: haematological relapse/progression, deaths without relapse/progression
- Cumulative incidence of aGVHD > grade II and extensive chronic GvHD
- Median and range for the number of CIK cell dose and for cumulative dose CIK cells/kg for all patients, children and adults

- Median and range for cumulative T cells/kg according donor type (MSD, MUD,MMFD) that patient requires in the study

Complete molecular response is defined as the molecular remission: the Minimal Residual Disease not detectable (MRD < 10^-6) and Mixed Chimerism MC < 1%.

Partial response is defined as no molecular remission but not haematological relapse. Non response is defined as haematological relapse without previous or complete response.

The median of PFS and OS time will be estimated. Kaplan-Meier estimates will be used to estimate PFS probability and OS probability. Log-rank test will be used as appropriate. For PFS will be considered as events: disease progression or relapse, death without relapse/progression and secondary neoplasm. For OS death from any cause will be considered an event.

Gray-Model will be used for cumulative incidences. Patients lost to follow-up without event will be censored at the date of their last follow up evaluation.

PFS, OS and cumulative incidences will be estimated after 1 year initiation of CIK cell therapy and after 1 year until the last CIK cell infusion.

If the data meet the necessary requirements, longitudinal analysis will be conducted to explore the improvement of hematologic and immune reconstitution of leucocyte, CD3-, CD4-, CD8-, CD56-, and CD14-positive cells until the first year after begin of the CIK cells therapy.

The dynamic of cytokine profile during cell infusion and tumor escape mechanisms following CIK cell infusion will exhibit in curves over the time.

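### Every planned GvHD analysis starts above grade II, so escalation interrupted by grade II acute GvHD goes uncounted, and the protocol's own withholding thresholds conflict

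*Protocol*

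**What the plan says.** **What is counted.** The Synopsis gives as a primary endpoint "The dose-limiting toxicity based on grade III or IV aGvHD", with extensive chronic GvHD as the other. Section 2.3 repeats this. Section 11 (Exploratory Endpoints) again names "The dose-limiting toxicity based on grade III or IV acute GvHD" and sets the safety endpoint as "Proportion of patients who become aGvHD > grade II or extensive chronic GvHD". The Analysis part of section 11 plans "Cumulative incidence of aGVHD > grade II and extensive chronic GvHD". The precision table for safety is also built on aGvHD above grade II.

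**What interrupts dosing.** Doses rise within each patient over three steps (section 3.1). Two thresholds are given:

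- From grade II: the Synopsis (Design) and section 3 say that with aGvHD at or above "grade II, the next scheduled infusion will not be administered". Section 3 lets infusions go on "provided that patients develop no more than grade I aGvHD". Section 3.1 has the same limit.
- Above grade II: section 5.4 and the stopping criteria in section 8.1 end infusions only when GvHD exceeds grade II.

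Separately, section 3.2 makes "No immunosuppression or steroids" a condition for the next infusion, and section 3.1 says that GvHD may be treated with such drugs.

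**What the trial is for.** The primary objective (Synopsis, section 2.1) is the safety and feasibility of increasing cell doses.

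**The concern.** An endpoint named dose-limiting toxicity would be expected to show how often toxicity limited the dose. Under the Synopsis, section 3 and section 3.1, grade II is enough to withhold the next infusion, yet grade II enters none of the listed proportions or cumulative incidences. A patient whose escalation halts at the first or second step because of grade II aGvHD is reported as having no DLT.

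What is at stake is the feasibility half of the primary objective. If grade II is not rare, the trial could end with a low DLT rate and no figure for the share of patients in whom GvHD prevented the planned escalation. The two thresholds make this worse: as written, sites could handle a patient with exactly grade II differently, and the analysis would not show it.

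**Working it through.** **1. The plan's own safety figures.** The exact (Clopper-Pearson) interval for x events in n patients has lower limit Beta(0.025; x, n-x+1) and upper limit Beta(0.975; x+1, n-x). With n = 20 and x = 1, 2, 4, 6, 8, 10, the 95% widths are 0.2475, 0.3046, 0.3793, 0.4239, 0.4483 and 0.4561. Section 11 prints 0.247, 0.305, 0.379, 0.424, 0.448 and 0.456. The 90% and 68% columns also agree to rounding. The arithmetic is sound; the issue is what is counted.

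**2. One patient traced through the passages.** Take a patient whose worst acute GvHD is grade II after the second infusion and who never develops extensive chronic GvHD.

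| Place in the protocol | Treatment of this patient |
|---|---|
| Synopsis (Design), sections 3 and 3.1 | Next infusion withheld |
| Sections 5.4 and 8.1 | Stopping threshold not reached |
| DLT (Synopsis, 2.3, 11) | No event |
| Safety proportion (11) | No event |
| Cumulative incidence (11) | No event |
| Two-weekly GvHD grading (3.1), AE page (6.1) | Graded and recorded |

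The data would exist, but no listed analysis uses them.

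**3. Whether the dose summaries fill the gap.** Section 11 plans the median and range of the number of CIK doses and of the cumulative dose. Section 8.1 also stops infusions on molecular response. A patient who responds after two infusions and one held by grade II after two infusions both contribute the value 2. The median cannot tell success from GvHD.

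**4. Size.** The protocol states no grade II rate, so this is illustration only. One patient in a group of 20 is 1/20 = 5 percentage points. Assume 2/20 with grade III-IV, that is 10% (exact 95% CI 1.2-31.7%), and add g patients with grade II as worst grade; the rate of grade II or higher is (2 + g)/20:

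| Assumed grade II patients | Grade II-IV | Exact 95% CI |
|---|---|---|
| 1 | 3/20 = 15% | 3.2-37.9% |
| 2 | 4/20 = 20% | 5.7-43.7% |
| 3 | 5/20 = 25% | 8.7-49.1% |
| 4 | 6/20 = 30% | 11.9-54.3% |

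The chance of at least one grade II patient among 20 is 1 - (1 - p)^20. This is 64%, 88% and 99% for assumed true rates p of 5%, 10% and 20%.

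**5. The only patient data in the protocol.** Section 1.5 reports 3 of 14 patients (21%) with grade III and 2 of 14 (14%) with mild acute GvHD, grade not given. If both mild cases were grade I, grade II or higher is 3/14, the same as grade III-IV. If both were grade II, it is 5/14 = 36% against 21%, a ratio of 5/3 = 1.7.

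**The case against.** The strongest defence is that grade III-IV is a coherent DLT. Sections 5.4 and 8.1 place the stop above grade II, exactly at the DLT threshold. The rule in the Synopsis speaks of the next scheduled infusion and can be read as a temporary hold. The 40% reference for donor lymphocyte infusion in section 11 is also for aGvHD above grade II, so endpoint and comparator match. The study is explorative, with descriptive analysis and no DLT decision rule. Extra tabulations are often left to an analysis plan. All of this stands as a reason to keep the DLT as it is.

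It does not close the gap. The clauses in sections 3 and 3.1 that allow continuation only at grade I or below read more strictly than a hold, and the protocol does not say which is meant. Even a temporary hold limits delivery when infusions are spaced 4-6 weeks apart and the study phase is capped at one year. The protocol itself fixes the threshold for each listed safety analysis, and none of them measures the delivery that its objective names.

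The bar on steroids and immunosuppressants names no grade. It would apply to a treated grade I patient too, so it is no evidence for a grade II threshold. It does show that GvHD can block an infusion by a second route.

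Four stronger inferences are tempting but unsupported:

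- *That grade II patients are reported as having no toxicity.* They are reported as having no DLT; section 3.1 has GvHD graded every two weeks, and section 6.1 puts all clinical adverse events on the CRF.
- *That the DLT should begin at grade II.* Nothing in the documents requires this, and it would break the match with the 40% reference.
- *That toxicity is understated several-fold.* Any such multiple depends on an assumed grade III-IV count, and section 1.5 allows ratios only between 1.0 and 1.7.
- *That DLT rates by dose step would be biased by selection.* No such rates are planned.

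**Conclusion.** The point holds in a limited form. The DLT, the safety proportion and the cumulative incidence count acute GvHD only at grade III-IV. Under the Synopsis, section 3 and section 3.1, escalation interrupted by grade II is therefore missing from every listed safety analysis, and the dose medians cannot recover it. Under sections 5.4 and 8.1 alone, the gap narrows to GvHD whose treatment bars the next infusion. The two sets of passages contradict each other on exactly grade II, and this review takes no view on which threshold is right.

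The size cannot be fixed from the protocol, because no grade II rate is given. It is 5 percentage points per such patient in each age group of 20. The 15-30% range rests on an assumed 2/20 with grade III-IV and 1 to 4 with grade II. The comparison with the 40% reference is unaffected. This is a worthwhile, inexpensive addition and does not invalidate the primary endpoint.

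**What to change.** 1. Reconcile the Synopsis, section 3 and section 3.1 with sections 5.4 and 8.1, so that one rule says what happens at exactly grade II and whether it is a hold or a permanent stop.
2. Keep grade III-IV acute GvHD as the DLT.
3. Add to section 11, for each age group:
   - the proportion (exact CI) and cumulative incidence of first aGvHD of grade II or higher;
   - the proportion of patients (exact CI) with at least one infusion withheld or stopped because of GvHD, counted separately from stops for molecular response, with the dose step reached.

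The cost is a few lines in section 11 and one more table. The grades are already collected at the two-weekly screening, so no new assessment is needed. The reason for each withheld infusion must be on the CRF; the CRF is not shown, so whether it already is cannot be checked. The downside for the sponsor is a less favourable toxicity picture.

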**Legend:**

( ), if applicable/optional

$x^1$ , monitoring for acute transfusion related toxicity while and up to 12 hours after CIK cell infusion, patients should be observed overnight within the context of an inpatient hospital stay. The study drug must be administered where emergency resuscitative equipment and personnel trained in the management of anaphylaxis are immediately available to treat systemic reactions under the direct supervision of a physician

$x^2$ , blood samples before, 1 hour, 1 and 2 weeks after CIK cell infusion for analyses of cytotoxic effects and tumor escape mechanisms

$x^3$ , monthly obligatory

$x^4$ , every 3 months

$x^5$ , optional

$x^6$ , once a year

$7$ , stop of CIK cell infusions: in case of molecular remission or if discontinuation criteria are reached,

If the patient does not reach molecular remission, administration of CIK cells will be stopped after the 8th CIK cell infusion.

## Glossary of Abbreviations

|        |   |                                              |
|--------|---|----------------------------------------------|
| aGvHD  | - | Acute Graft-versus-Host Disease              |
| AE     | - | Adverse Event                                |
| ALL    | - | Acute Lymphoblastic Leukemia                 |
| Allo   | - | Allogeneic                                   |
| AML    | - | Acute Myelogenous Leukemia                   |
| BM     | - | Bone Marrow                                  |
| CC     | - | Complete Chimerism                           |
| cGvHD  | - | Chronic Graft-versus-Host Disease            |
| CIK    | - | Cytokine induced killer                      |
| DFS    | - | Disease free survival                        |
| DLI    | - | Donor Lymphocyte Infusion                    |
| ECG    | - | Electrocardiography                          |
| GMP    | - | Good Manufacturing Process                   |
| GSC    | - | Glucksberg Seattle Score                     |
| GvHD   | - | Graft versus Host Disease                    |
| HBs AG | - | Hepatitis s Antigen                          |
| HCV    | - | Hepatitis C Virus                            |
| HIV    | - | Human Immunodeficiency Virus                 |
| HLA    | - | Human Leukocyte Antigen                      |
| IFN    | - | Interferon                                   |
| Ig     | - | Immunoglobulin                               |
| IL     | - | Interleukin                                  |
| IMP    | - | Investigational Medicinal Product            |
| IZKS   | - | Interdisziplinäres Zentrum Klinische Studien |
| KIR    | - | Killer Cell Immunoglobulin Like Receptor     |
| MC     | - | Mixed Chimerism                              |
| MDS    | - | Myelodysplastic syndrom                      |
| MHC    | - | Major Histocompatibility Complex             |
| MRD    | - | Minimal Residual disease                     |
| NK     | - | Natural killer                               |
| NKG2D  | - | Activatory NK Cell Receptor                  |
| PB     | - | Peripheral Blood                             |
| PBMC   | - | Peripheral Blood Mononuclear Cells           |
| PCR    | - | Polymerase Chain Reaction                    |

|       |   |                                                |
|-------|---|------------------------------------------------|
| RMS   | - | Rhabdomyosarcoma                               |
| RT    | - | Reverse Transcriptase                          |
| SAE   | - | Severe Adverse Event                           |
| SCT   | - | Stem cell transplantation                      |
| STR   | - | Short Tandem Repeats                           |
| SUSAR | - | Suspected Unexpected Serious Adverse Reactions |
| TCR   | - | T cell receptor                                |
| TPHA  | - | Treponema pallidum Haemagglutinationstest      |
| TRM   | - | Treatment Related Mortality                    |
| TKI   | - | tyrosine kinase inhibitor                      |
| WT    | - | Wilms Tumor                                    |

## Surface Antigens

|          |   |                  |
|----------|---|------------------|
| CD3      | - | T Cell           |
| CD4      | - | Helper T Cell    |
| CD8      | - | Cytotoxic T Cell |
| CD14     | - | Monocyte         |
| CD34/ 33 | - | Stem cell        |
| CD56     | - | NK Cell          |

# 1 Introduction

## 1.1 Allogeneic Stem Cell Transplantation and Cellular Therapy

In acute lymphoblastic (ALL) and myeloid (AML) leukemia patients as well as in adult myelodysplastic syndrome (MDS) patients with chemotherapy resistant diseases allogeneic hematopoietic stem cell transplantation (SCT) will be performed according to the respective study protocols. Moreover, allogeneic SCT includes upfront therapy for pediatric patients with MDS, and will also be offered for therapy-related MDS and AML, which might occur as complications of chemotherapy. This complication often presents after a median latency period of approximately four to five years after chemotherapy treatment.

Standard therapy of BCR-ABL positive leukemias above all includes treatment with tyrosine-kinase inhibitors (TKI).

Hence, allogeneic SCT has become an established method in the treatment of above-mentioned high-risk leukemia and myelodysplastic syndromes (MDS). In both groups, the therapeutic success is limited by patients' relapse. Once a stem cell recipient relapses, further therapeutic options are limited. For instance, re-induction chemotherapy may cause remission with acceptable toxicity and a possible delay in time to relapse but therapeutic effects are transient. Relapsed patients with good performance status and without severe comorbidity might be considered for a second allogeneic SCT, if relapse occurs after day 300 in adult and after day 200 in pediatric patients. In these patients, second allogeneic SCT may provide a small curative chance of 20% but this approach entails a high rate of morbidity and mortality.

Another treatment option may include taper of immunosuppressive medications followed by donor lymphocyte infusion (DLI), which can generate a graft versus leukemia effect (GvL), but is associated with an increased risk of graft versus host disease (GvHD). Moreover, the success rate of this approach is less than 15%.

To improve outcome of leukemia and MDS patients after allogeneic SCT, the detection of impending relapse or early stages of relapse is necessary, as this status is a precondition for further therapeutic options. Predictors of relapse after allogeneic SCT have been monitoring for minimal residual disease (MRD), and BCR-ABL as well as loss of donor cell chimerism.

Evidence was presented, that MRD or MC status in leukemia and MDS patients in principle could be treated by DLI. However, DLI is only efficacious for defined diseases and is of limited value when initiated during overt relapse. Moreover, the high T cell doses required for DLI raise the risk of GvHD.

Due to the risk of GvHD, strategies to prevent post-SCT relapse have been developed including vaccination and targeted immunologic interventions (i.e. small molecule inhibitors, mAbs and chimeric antigen receptor T cells). These treatments have mostly been evaluated in vitro or in early phase I/II studies and require the presence of leukemia specific antigens. In contrast, cytokine induced killer (CIK) cells with reduced alloreactive potential are broadly applicable against a variety of hematological malignancies including ALL, AML and MDS. Sequential infusions of interleukin (IL)-15 expanded CIK cells may therefore prevent relapse with reduced risk of causing GvHD in patients with leukemia or MDS being at high risk for relapse after allogeneic SCT. As immunotherapeutic intervention is most promising in the setting of low leukemic cell burden CIK cells will be administered in patients with impending relapse indicated by MRD, BCR-ABL or MC in this trial.

